## Abstract

**Background:**

Adapting promising health care interventions to local settings is a critical component in the dissemination and implementation process. The Veterans Health Administration (VHA) rural transitions nurse program (TNP) is a nurse-led, Veteran-centered intervention designed to improve transitional care for rural Veterans funded by VA national offices for dissemination to other VA sites serving a predominantly rural Veteran population. Here, we describe our novel approach to the implementation and evaluation = the TNP.

**Methods:**

This is a controlled before and after study that assesses both implementation and intervention outcomes. During *pre-implementation*, we assessed site context using a mixed method approach with data from diverse sources including facility-level quantitative data, key informant and Veteran interviews, observations of the discharge process, and a group brainstorming activity. We used the Practical Robust Implementation and Sustainability Model (PRISM) to inform our inquiries, to integrate data from all sources, and to identify factors that may affect implementation. In the *implementation phase*, we will use internal and external facilitation, paired with audit and feedback, to encourage appropriate contextual adaptations. We will use a modified Stirman framework to document adaptations. During the *evaluation phase*, we will measure intervention and implementation outcomes at each site using the RE-AIM framework (Reach, Effectiveness, Adoption, Implementation, and Maintenance). We will conduct a difference-in-differences analysis with propensity-matched Veterans and VA facilities as a control. Our primary intervention outcome is 30-day readmission and Emergency Department visit rates. We will use our findings to develop an implementation toolkit that will inform the larger scale-up of the TNP across the VA.

**Discussion:**

The use of PRISM to inform pre-implementation evaluation and synthesize data from multiple sources, coupled with internal and external facilitation, is a novel approach to engaging sites in adapting interventions while promoting fidelity to the intervention. Our application of PRISM to pre-implementation and midline evaluation, as well as documentation of adaptations, provides an opportunity to identify and address contextual factors that may impede or enhance implementation and sustainability of health interventions and inform dissemination.

## Background

Patients are at high risk for adverse events during the transition period from hospital to home [1, 2]. The transition home presents challenges such as adjusting to new or changed medications, understanding disease management strategies, and learning home care routines. “Bridging” (i.e., pre- and post-discharge) interventions to improve transitional care practices reduce hospital readmissions [3]. These interventions focus on creating an “ideal” transition of care, which includes preparing patients for discharge with thorough education about self-care, ensuring the completion of medication reconciliation, arranging for any home care needs, and organizing appropriate follow-up [3–9]. Improving the transition from hospital to home is especially important in high-risk cohorts [3, 10], such as the elderly or those who live in a rural setting.

Rural Veterans are a high-risk cohort as they face barriers in nearly all aspects of an ideal transition in care. One such barrier relates to the structure of the Veterans Health Administration (VA) healthcare system. The VA is organized in a hub and spoke system, with large hospitals in urban areas and affiliated smaller clinics in rural areas. This structure leads to unique challenges for rural Veterans transitioning back to their primary care provider, such as difficulties with medication reconciliation between VA facilities, medication gaps due to limited availability of specialized medications in rural areas, inadequate discharge plans, lack of communication between tertiary hospitals and rural Patient Aligned Care Team (PACT) sites, and missed follow-up appointments with primary care providers (PCPs) [11]. In this paper, we describe the dissemination and implementation plan for the rural Transitions Nurse Program (TNP), a nurse-led and Veteran-centered intervention designed to address these transitional care gaps and improve post-discharge outcomes for rural Veterans hospitalized at tertiary VA sites.

The dual goals of this project are to (1) improve transitions and reduce hospital readmissions for rural Veterans hospitalized at tertiary VA facilities, and (2) contribute to the field of implementation science through a robust application of the PRISM framework at every stage from pre-implementation contextual assessment, to implementation and adaptation, to evaluation. The PRISM framework has been used to assess site context in a number of studies [12, 13], but to our knowledge, it has not been used to organize and integrate data from multiple sources or in an iterative manner to guide implementation and evaluation in successive waves. This work will address a gap in the literature on the use of PRISM to guide implementation. It will test the utility of PRISM to guide scale-up efforts of an intervention to diverse settings and provide an example of an innovative diffusion process in the VA.

## Methods

### Description of intervention

The TNP is an intervention carried out with a Transition Nurse (TN) in collaboration with a hospitalist site champion at each intervention site. The intervention is based on the Ideal Transitions of Care (ITC) framework [3] and consists of four core components. These are (1) pre-discharge assessment of patient understanding of self-care, medications, supports for post-discharge care, and obtaining a follow-up appointment; (2) structured post-discharge interactive communication between the hospital and primary care team alerting the primary care team of discharge; (3) a follow-up call to the patient within 48 to 72 h of discharge to confirm attendance to the follow-up appointment with the PCP, reinforce medication and self-care education provided at discharge, and assess symptoms and concerns; and (4) build knowledge and capacity at both the tertiary and primary care site to deliver improved care to future rural Veterans. The TNP was piloted in Denver between 2014 and 2016 with encouraging results such as reduced hospital readmissions and reduced costs relative to a control population [11]. Based on the success of the pilot, the TNP was funded by the VA Office of Rural Health with the support of the Veterans Health Administration (VHA) Office of Nursing Services for expansion to additional tertiary VA sites over the next 5 years.

### Intervention and study design

We will use the Practical, Robust, Implementation, and Sustainability (PRISM) model [14] to inform the both implementation and evaluation of TNP. PRISM is ideal for guiding our multi-site implementation effort because it accounts for multi-level effects; it builds on several Implementation Science frameworks and can guide pre-implementation, implementation, and evaluation. Several studies show that the adoption, implementation, and sustainment of interventions are related to how well the intervention is integrated into the local context [12–16]. We will assess PRISM domains using convergent mixed methods, collecting both quantitative facility-level data, and qualitative data. We will use PRISM in each phase of our intervention: pre-implementation, implementation, and evaluation. Figure 1 shows the flow of project phases.

**Fig. 1 Fig1:**
[figure not shown]
TNP flow chart. This figure illustrates how each stage of the TNP intervention informs subsequent stages. Our pre-implementation evaluation of intervention recipients informs adaptations to the intervention. Evaluation of adaptations and intervention outcomes inform preparation for the next cycle of implementation

This is a type II hybrid study, which tests both intervention outcomes and the implementation strategy [17]. TNP implementation will occur in waves, enrolling additional sites every 12 months. Each wave of implementation will follow three stages: pre-implementation training and evaluation, implementation, and outcome evaluation. It is important to distinguish the evaluation components of pre-implementation and implementation from the final outcome evaluation. Pre-implementation evaluation will be used to evaluate the implementation strategy and tailor the intervention to each site, formative midline evaluation 6 months after implementation will measure the initial intervention outcomes and provide performance feedback to each site, whereas summative outcome evaluation will measure the overall success of the program outcomes and implementation strategy at each site, and will be used to adapt future waves of implementation.

### Context

In the first wave of implementation, the program will be implemented at five sites (2017), one site from each of five geographic VA “regions,” the North Atlantic Region, the Southeast Region, the Midwest Region, the Continental Region, and the Pacific Region. These are tertiary hospital sites that treat more than 1000 rural Veterans annually, had leadership willing to sign a letter of support, and an active hospitalist program that cares for the majority of medical inpatients at the tertiary site. Prior to the second wave of implementation, we will evaluate implementation at the first five sites to test the utility of our implementation strategy. In subsequent waves, the Office of Rural Health will use a national solicitation of applicants for participation in the TNP through a formal application process. Sites that serve large rural populations will be encouraged to apply through targeted promotional materials to hospital leadership.

### Description of implementation strategy

We will conduct pre-implementation site assessments before rolling out the program at each expansion site. Our implementation strategy combines robust pre-implementation work with internal and external facilitation, and audit and feedback.

#### Pre-implementation

During the pre-implementation phase, we will collect qualitative contextual data to (1) understand the current process for transitioning rural Veterans back to their PCP after an inpatient hospitalization at a VHA tertiary medical center, (2) identify and highlight the impact of factors encapsulated in the PRISM framework that may enhance or discourage the implementation of TNP at participating sites, and (3) use these data to facilitate implementation, document adaptations to the program, and enhance sustainability of the intervention and its implementation. In addition, we will meet with site leadership and identify a hospitalist champion as an internal facilitator. A hospitalist was chosen for this role to provide a link between inpatient and outpatient settings and to help troubleshoot clinical problems with enrolled patients. Each site will identify a cohort of rural patients to enroll in the program and modulate the TN workflow to avoid overlap with other transition of care practices.

Qualitative methods include key informant interviews, process mapping, as well as site visits with adapted ethnographic observation and a written group brainstorming activity (brainwriting). Key informant interviews and process mapping interviews with providers and administrators will begin prior to pre-implementation site visits. Table 1 summarizes how we use these methods to measure PRISM domains in our pre-implementation evaluation.

**Table 1 Tab1:** Assessing PRISM domains to understand context for implementation

PRISM domain	What we are assessing	Data collection technique
Organizational perspective	▪ Current transition process ▪ How TNP fits in the broader organization ▪ Contextual factors that may impede or enhance TNP implementation	▪ Process mapping interviews ▪ Key informant interviews ▪ Adapted ethnography ▪ Brainwriting activity ▪ VA all employee survey, PACT survey, Pi2 index, inpatient data (IPEC) ▪ Implementation readiness survey
Patient perspective	▪ Current transition process ▪ Satisfaction with transition process ▪ Receptiveness to TN role	▪ Veteran interviews ▪ Adapted mini ethnography
External environment	▪ VA regulations ▪ Existing VA infrastructure (CPRS) ▪ Political climate and funding	▪ Key informant interviews ▪ Brainwriting activity
Implementation and sustainability infrastructure	▪ Existing processes and systems ▪ Current transition process ▪ Existing relationships and collaboration ▪ Plan for sustainability	▪ National level VA quantitative data ▪ Key informant interviews
Organizational characteristics	▪ Management support ▪ Shared goals and cooperation ▪ Inter-facility communication	▪ National level VA quantitative data ▪ Process mapping ▪ Brainwriting ▪ Key informant interviews
Patient characteristics	▪ Demographics ▪ Rural veteran readmission dates	▪ Key informant ▪ Brainwriting ▪ Veteran interviews ▪ Quantitative data on 30-day readmissions

We will employ process mapping to understand the current discharge process for rural Veterans and inform the implementation process [18]. We will validate process maps using adapted ethnographic observations on-site visits [19]. During adapted ethnographic observation, qualitative analysts will join medical teams on rounds and observe the patient discharge process. Team members will collect information on the process, interactions among providers and between providers and patients, and contextual information on the atmosphere. Process maps will also aid in return on the investment (ROI) analyses by identifying each role involved in the discharge process, the steps in the process, and time and resources required to complete each step in the discharge process.

Key informant interviews with providers at VA tertiary hospitals and rural PACT clinics will identify attitudes and beliefs, initial reactions to the TNP, barriers and facilitators to implementation of the TNP, and participant perspectives on the potential value of the program. Interviews will be summarized for each site and used to inform site visit data collection. In particular, interviews will determine which areas of the discharge process need clarification or confirmation and identify remaining questions.

Finally, during pre-implementation site visits, we will conduct a brainwriting activity [20, 21]. The brainwriting activity will be used to clarify the rural patient discharge process at each site, to identify perceived failure points in the implementation of TNP and to consider strategies to overcome these barriers. Site visits provide the opportunity to verify what we learn in key informant and process map interviews.

Pre-implementation data will inform adaptations to the intervention. We will provide sites with initial feedback from our interviews and observations within 1 week of the site visit using rapid qualitative analysis techniques [22, 23]. This will allow sites to begin planning for implementation. Additionally, cross-site barriers and facilitators will be identified and discussed with site transition nurses and hospital champions during pre-implementation training.

### Transition nurse training

Transition nurses from each site will be trained in their role prior to implementation. Transition nurses will complete care coordination and transitions management (CCTM) online training and a 2-day in-person training session in Denver. CCTM is conducted through a course offered by the American Academy of Ambulatory Care Nursing (AAACN) and was created from a consensus statement of the AAACN about the core competencies for care coordination [24]. The in-person training will take place at the Center for Advancing Professional Excellence (CAPE) at the University Of Colorado School Of Medicine in Denver, CO. This 2-day training will focus on learning and practicing relationship-centered communication skills and goal-based effective feedback techniques, through utilization of standardized patients. The skills-based training is interactive, experiential, and grounded in feedback. Training will discuss skills for initiating and maintaining relationships, as well as sharing information and negotiating a mutual plan of action. Pre- and post-training surveys will assess nurse satisfaction and perceived change in confidence and knowledge after training.

#### Implementation

Our implementation strategy uses internal and external facilitation [25] and audit and feedback [25, 26] to encourage real-time adaptation of the intervention to each site. In our intervention, external facilitation will be conducted by a team in Denver. The primary investigator in Denver (RB) will meet with individual site leadership and leverage relationships with the Office of Rural Health and the Office of Nursing Services. Internal facilitation is conducted by the hospitalist champion, who will receive data from the team in Denver and have an on-the-ground role in establishing successful implementation of the program. Each site must complete the four core components of the intervention but will individualize the intervention by determining how the intervention best fits their needs and local context. For instance, each site will be responsible for identifying the high-risk rural patient population they will enroll, as each site has more rural Veteran hospitalizations (more than 1000 annually at each site) than the transition nurse can likely enroll (pilot data suggests enrollment of 250–350 rural Veterans annually).

In the first month of implementation, the TN at each site will participate in a regular teleconference with facilitators in Denver to identify barriers to intervention uptake and formulate solutions. The teleconference will serve to support the TNs as they begin enrolling patients in the program, to continually identify barriers to the program and to promote a community of practice. The Denver team will conduct a site visit 6 months after the initial implementation on TNP. The purpose of this site visit is to understand local context in order to better assist with remaining implementation barriers and to evaluate implementation fidelity. This is part of our audit and feedback strategy. By monitoring implementation at each site and assessing barriers as they arise, we will collect actionable data to share with the hospitalist champions that can be used to customize the TNP to each site. For example, we will share with each site the number of Veterans admitted, the number of Veterans who receive all components of the intervention, the time required to enroll Veterans in the program, and hospital readmission rates on a monthly to quarterly basis.

In addition, the facilitators in Denver will also provide contextual interventions to address problems that may arise during implementation (e.g., problems identified in teleconferences and site visits). Possible interventions for barriers include targeted capacity building, team building, encouraging and facilitating communication, reaching out to leadership to enlist support for the intervention, and providing knowledge sharing opportunities (e.g., best practices).

We will ask the first five sites to facilitate implementation at the second wave of sites using a “train the trainer” approach. We will create a manual that encapsulates lessons learned, common barriers to implementation, and solutions to these barriers and ask the first five sites to consider using this manual to “train” the new sites in their region.

### Implementation outcomes

We will assess both intervention outcomes and implementation outcomes [27, 28]. We will use the RE-AIM framework [29] to measure implementation outcomes (see Table 2).

**Table 2 Tab2:** RE-AIM measures in the rural transition nurse program

RE-AIM measures	TNP definition	Measurement
R—Reach	▪ Proportion of eligible rural Veterans enrolled at each site	▪ Number of Veterans enrolled each month ▪ Proportion of eligible Vets enrolled
E—Effectiveness	▪ Primary outcome is emergency department visits and hospitalizations in the 30 days following index discharge; Cost of utilization (ED/hospital); Satisfaction of Veterans and providers	▪ Hospital readmission rates ▪ Return on Investment ▪ Provider satisfaction surveys ▪ Qualitative semi-structured interviews ▪ Veteran satisfaction surveys
A—Adoption	▪ Proportion of inpatient providers that refer eligible Veterans to the TN for enrollment in the TNP ▪ Proportion of PACT providers that complete communication (*close communication loop through Lync, email, phone*) for care coordination with the TN as part of the TNP	▪ Number of Veterans enrolled each month ▪ Proportion of eligible Vets enrolled, 6 months after enrollment begins, and 1 year after enrollment begins
I—Implementation	▪ Evaluating what components of the manual and toolkit have been implemented and how they have been adapted (using Stirman framework)	▪ Regular phone calls with TNs will identify adaptations, barriers, and facilitators to implementation ▪ Survey to measure TN and Hospital Champion view of program ▪ Observational assessment of TN competency and adherence to TNP core components, as well and pre and post-test ▪ Semi-structured interviews with TNs, Hospital Champions, inpatient and PACT clinicians, and Veterans to identify internal and external factors that affect TNP implementation, as well as barriers and facilitators to implementation ▪ Measurement of adaptations using real-time tracking with and adapted Stirman framework
M—Maintenance	▪ Funding or expansion of TN role at expansion sites after 3 years of funding	▪ Return on investment ▪ Continued use and improvement of TNP program

We will complement RE-AIM with the use of an adapted version of the Stirman adaptation and modification framework [30] to systematically document program modifications during implementation. Our pragmatic approach emphasizes the need for careful balance between fidelity to core program elements and modifications of peripheral program components (i.e., those components that are not essential to achieving consistent program outcomes) to local circumstances and preferences. The adapted Stirman framework includes tracking who makes modifications, what is modified, at what level of delivery, context modifications, and the nature of context modifications. Using this information in combination with intervention outcome measures, we will determine which parts of the intervention are necessary for success, in order to inform subsequent waves of implementation and to ensure sustainability in present and future contexts.

All qualitative data will be managed and coded using *Atlas.ti* [31] according to PRISM domains. A priori codes were developed through group discussion; additional codes that emerge will be applied to all previously coded manuscripts until saturation is reached [32–34]. Intercoder reliability will be conducted through team-based consensus building; qualitative analysts will independently code the same three transcripts and then discuss points of divergence and convergence. These discussions and coding of additional transcripts will continue until the group reaches consensus on the code meaning and application. Investigators with expertise in qualitative methods and implementation science (JJ, BR) will moderate these discussions.

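### Table 2 defines Adoption by providers but measures it with Veteran enrolment, repeating Reach; no measure given in the article yields either stated Adoption proportion

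*Protocol article*

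**What the plan says.** The article uses RE-AIM to measure implementation outcomes, and Table 2 (Implementation outcomes) gives each domain a definition and a measurement.

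- **Reach, definition:** "Proportion of eligible rural Veterans enrolled at each site".
- **Reach, measurement:** "Number of Veterans enrolled each month ▪ Proportion of eligible Vets enrolled".
- **Adoption, first definition:** "Proportion of inpatient providers that refer eligible Veterans to the TN for enrollment in the TNP".
- **Adoption, second definition:** "Proportion of PACT providers that complete communication" with the TN; the table names the channels that count.
- **Adoption, measurement:** the monthly enrolment count again, and "Proportion of eligible Vets enrolled, 6 months after enrollment begins, and 1 year after enrollment begins".

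Three other items come near the subject. The Implementation row of Table 2 lists "Semi-structured interviews with TNs, Hospital Champions, inpatient and PACT clinicians, and Veterans to identify internal and external factors that affect TNP implementation" and "Observational assessment of TN competency and adherence to TNP core components". The Implementation subsection, on audit and feedback, says that sites will be told "the number of Veterans who receive all components of the intervention".

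**The concern.** The two columns of the Adoption row do not describe the same quantity. The definitions ask what share of providers take part; the measurements say what share of Veterans are enrolled. Both columns are stated, so this is not detail that a condensed article has left to a fuller document.

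This is a type II hybrid study, which tests the implementation strategy as well as the intervention. The Discussion says that external facilitators will pass RE-AIM measures to the internal facilitators so that sites can make targeted changes. If Adoption is reported from the listed measurements, a site whose referrals come from a few physicians looks the same as one where referral is general practice, and a site whose PACT teams do not respond looks the same as one whose teams do. Communication between hospital and primary care is one of the four core components. The Discussion also presents the nurse's relationship with rural PACT staff as what the program adds to an existing VA transitional care program.

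**Working it through.** The article gives no figure for Adoption to reproduce. The check compares the rows, searches for a substitute elsewhere, and asks whether enrolment could serve as a proxy.

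**1. The rows side by side (Table 2)**

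| Item | Unit | Numerator | Denominator |
|---|---|---|---|
| Reach, as defined | Veteran | enrolled | eligible |
| Reach, as measured | Veteran | enrolled (also as a monthly count) | eligible |
| Adoption, definition 1 | inpatient provider | those who refer | inpatient providers |
| Adoption, definition 2 | PACT provider | those who complete communication | PACT providers |
| Adoption, as measured | Veteran | enrolled (also as a monthly count) | eligible, at 6 months and 1 year |

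Adoption definitions with a matching measurement: 0 of 2. Adoption measurements that repeat Reach apart from time points: 2 of 2.

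**2. Possible substitutes elsewhere in the article**

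- The clinician interviews yield barriers and facilitators, not a proportion of providers.
- The observation of competency and adherence assesses the TN, not the referring or PACT providers.
- The audit count of Veterans who receive every component may reflect communication at patient level, but has no provider numerator or denominator.
- The provider surveys in the Effectiveness row measure satisfaction.

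Each of the first three touches on referral or communication. None gives either Adoption proportion.

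**3. Can enrolment act as a proxy?**

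Inputs, from the Implementation subsection: more than 1000 rural Veteran hospitalizations a year at each site, and pilot-based enrolment of 250–350 Veterans a year. The article says this is more than the nurse can likely enroll.

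- Lower end: 250 / 1000 = 25%.
- Upper end: 350 / 1000 = 35%.

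Because hospitalizations exceed 1000, these percentages are ceilings at the stated enrolment levels. They assume that all rural hospitalizations form the denominator; a narrower site-defined eligible group would raise them. In either case, the nurse's capacity and the site's choice of cohort help to set the enrolment proportion, so it can stay level whether few or many providers refer.

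The same follows without an assumed staff size. Let P be the inpatient providers at a site, R the distinct providers who refer, and E the Veterans enrolled, with P no larger than E. If every enrolment starts with a provider's referral (an assumption; the article does not say so), R can be anything from 1 to P. Definition 1, R/P, then ranges from 1/P to 1 at the same E. If the nurse also finds patients directly, the lower end falls to 0.

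For definition 2, completing communication is a separate act by the PACT provider, which an enrolment count does not record. With E fixed, that proportion can lie anywhere from 0 to 1.

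**The case against.** The strongest reply is that this is a condensed article. The definitions already name two countable proportions, data capture belongs in a full protocol or analysis plan that is not shown, and the measurement cell may be a slip carried over from the Reach row. Authors who follow the definition column would report provider proportions. Part of this stands, and it rules out several stronger readings.

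- A reader might infer that provider referral and PACT response will never be measured. The article cannot show that; a fuller document may collect them. It shows only that no measure it specifies yields them.
- A reader might infer that PACT communication has no measure at all. That goes too far. The count of Veterans who receive all components should take in communication at patient level, since it is a core component, and the TN's adherence to core components is observed. What is missing is a provider proportion.
- A reader might infer that reported Adoption is bound to equal Reach. That holds only if the measurement column is followed literally, and even then Adoption adds two time points.
- A reader might infer that Adoption is a principal implementation outcome. Table 2 does not rank the five domains.

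The reply does not remove the mismatch. If the cell is a slip, it still states the wrong measure, and anyone working from Table 2 would compute it.

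**Conclusion.** The point holds as an inconsistency within one table row. The Adoption measurements do not correspond to the Adoption definitions and, apart from time points, repeat Reach. Used as written, Adoption would add little to Reach and could not show how widely inpatient providers refer or PACT providers respond.

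The row comparison rests on the table alone. The capacity argument rests on the article's own figures, with all rural hospitalizations assumed as the denominator for the 25–35%. The article gives no provider numbers, so the effect on a reported Adoption value cannot be sized beyond the ranges shown.

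This should be corrected, but its reach is limited: it concerns one RE-AIM domain, and the primary 30-day readmission and ED analysis does not depend on it.

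**What to change.** Replace the two Adoption measurements with the proportions already defined, each reported by site at the 6-month and 1-year points that the row already sets:

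1. distinct inpatient providers who referred, divided by inpatient providers caring for eligible rural Veterans;
2. distinct PACT providers who completed communication, divided by PACT providers contacted by the TN.

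Other denominators would also fit the definitions; what matters is that one is fixed in advance and used at every site. Keep the enrolment count and the enrolment proportion under Reach.

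The cost is more than a change of wording. The referring provider and loop closure must be recorded for each enrolled Veteran, and a provider denominator must be obtained for each site. Since capacity limits enrolment, the plan should also say whether referrals that do not lead to enrolment count; if they do, those must be logged too. The primary analysis does not change.
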